**Methods/Design:**

A randomized controlled trial (RCT) nested within a 13-month longitudinal cohort study. The RCT (conducted over 12 months) tests the effectiveness of a novel, early, home-based, personalized program (compared with no intervention) in arresting or slowing FD.

TRIIFL focuses on older adults living independently in the community, who have not yet had a serious health event, yet are potentially on the cusp of FD. Participants in the longitudinal cohort study will be recruited as they present to one large tertiary hospital Emergency Department, providing they are not subsequently admitted to a ward. Sample size calculations indicate that 570 participants need to be recruited into the longitudinal study, with 100 participants randomized into the trial arms.

Measures from all subjects will be taken face-to-face at baseline (recruitment), then subsequently by telephone at one, four, seven and thirteen months later. Measures include functional abilities, quality of life, recent falls, mobility dependence, community supports and health service usage. Specific to the nested RCT, the quality of life tool (SF12) applied at one month, will identify individuals with low mental component quality of life scores, who will be invited to enter the RCT.

Assessors will be blinded to RCT arm allocation, and subjects in the RCT will be blinded to the intervention being received by other subjects.

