### Sample size considerations

To date, there is scant research that has established the effectiveness of any community-based person-centered intervention program that alerts older people who are on the cusp of FD to impending FD and provides means to assist and support them. We drew the likely effectiveness of the proposed intervention program from research on early intervention programs for at-risk older people who are in hospital or rehabilitation units. This included an Australian study [47] (significant improvement in goals and functioning) and a Dutch study [48] (effect size 0.25). We acknowledge that this research may not be readily generalizable to estimate effectiveness of the intervention in our reference population; however, it is the best available evidence for sample size calculation.

Our nested RCT study sample size was further calculated on minimal differences in iADLs and SF12 scores, expected at three-month follow-up from our pilot data [37]. These estimates are based on the three-month follow-up distributions for iADLs and SF-12. Parameters of power were set at π = 80% (1-β), with α = 5%. For iADLs, we identified that a minimum absolute effect size of 1.2 would be needed for participants to have dropped by at most 1 point on the Lawton scale (the Lawton definition of FD requires a drop of 2+ points on the scale). Thus, a minimum sample size of N_IADL_ = 50 per RCT cohort would be required (total 100). For the MCS domain of SF-12, a minimum absolute effect size of 4.3 would need to be observed, to put all scores above or equal to the median value, giving sample size of N_MCS_ = 30 per RCT cohort (total 60). Similarly for the PCS domain of SF-12, the minimum absolute effect size of 12.2 gives a sample size of N_PCS_ = 6 per RCT cohort (total 12). We require significance to be determined both clinically and statistically, so over-sampling is not of concern and, therefore, we choose the highest sample size (N_IADL_) of N = 50 per RCT cohort (100 total) at three months RCT follow-up (four months from ED recruitment). Thus, our continuing RCT sample at three months will reflect 100 individuals with low SF12-MCS (randomized 50 each into intervention and control arms), and 100 individuals with high SF12-MCS who will simply be followed-up.

To provide the nested RCT cohort sample, there are specific considerations which will influence the number of individuals invited to participate in Study 1:

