The three study cohorts will be assessed at time of allocation into a study arm (one-month after recruitment) for homogeneity in key socio-demographic characteristics and immutable factors (for example, gender, age, schooling, postcode, diagnosis) and all outcome measures (including the percentage of ‘frequent flyers’ in each arm). We previously reported this as one or more ED contacts per month over the preceding 12 months [33,34].

Change over time in each outcome measure will be calculated using repeated measures analysis of variance (ANOVA) models, with study contact point, cohort (1, 2, or 3) and key demographic features as independent variables. Partial Least Squares (PLS) models using pathway analysis will be applied to the multiple outcome, immutable and mutable independent variables at each time point, to determine different spatial arrangements and the significant factors which impact on data clusters.

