### Hypotheses

As shown in Figure 2, our hypothese are:

1. The observed cohort will not demonstrate FD over the following 12 months in any FD measure.

2. The low SF12-MCS, no treatment cohort will demonstrate significant FD in any one or more outcome measures, taken over the next three months, when compared to their baseline recruitment status.

3. The low SF12-MCS, intervention cohort will show no FD (comparable findings to the observed cohort) over the next 12 months.

4. Additionally, those individuals in the low SF12-MCS, no treatment cohort who demonstrate significant FD at three months follow-up, and who access ‘rescue’ intervention (see Section on Ethics), will show an attenuated rate of FD over the following twelve months, compared with the rate they exhibited in the first three months.

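### None of the four hypotheses compares the two randomised arms, and the planned ANOVA does not name that contrast as the basis for the effectiveness conclusion

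*Protocol article*

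**What the plan says.** The abstract (Methods/Design) says the RCT "tests the effectiveness of a novel, early, home-based, personalized program (compared with no intervention) in arresting or slowing FD". The Hypotheses section then lists four statements:

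- **Hypothesis 1** concerns the observed (high SF12-MCS) cohort alone, over 12 months.
- **Hypothesis 2** expects the no-treatment arm to show significant decline in one or more measures, "taken over the next three months, when compared to their baseline recruitment status".
- **Hypothesis 3** expects that the low SF12-MCS "intervention cohort will show no FD (comparable findings to the observed cohort) over the next 12 months".
- **Hypothesis 4** sets controls who decline and take up rescue care against their own earlier rate.

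Under Analysis of data from Studies 1 and 2, change in each outcome is to be analysed by repeated measures ANOVA "with study contact point, cohort (1, 2, or 3) and key demographic features as independent variables". No contrast within the cohort factor is named. Under Sample size considerations the RCT is sized at three months after randomisation with "50 per RCT cohort would be required (total 100"), alongside "100 individuals with high SF12-MCS who will simply be followed-up".

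**The concern.** Randomisation protects one comparison: intervention against no treatment. The hypotheses do not use it. They put one randomised arm against its own past and the other against a group formed by a different SF12-MCS score.

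- **The references differ.** Hypothesis 2 uses the value at ED recruitment, one month before allocation. Hypothesis 3 uses the observed cohort, which the one-month cut point of 55 separates from the trial arms.
- **The horizons differ.** They are 3 months and 12 months.
- **The standards of proof differ.** Hypothesis 2 needs a significant decline on any measure. Hypothesis 3 is supported by finding no decline or no difference, with no margin to say how close is comparable.

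A significant change in one arm and none in the other does not show that the arms differ. If the effectiveness conclusion were read off these statements, an inert programme could appear to work. A real between-arm benefit could also be missed, if the controls' own decline is not significant by three months.

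**Working it through.** **1. Inputs and the plan's own figure.** From Sample size considerations: "Parameters of power were set at π = 80% (1-β), with α = 5"%, an iADL effect of 1.2 points, 50 per randomised arm and 100 observed. Sidedness is not stated; two-sided is assumed.

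The usual formula is n per arm = 2 × (1.96 + 0.84)² × SD² / 1.2². No SD is given, so 50 per arm cannot be reproduced independently. Solving backwards gives SD = 2.14, and putting 2.14 back in returns 50, which is circular.

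**2. What each hypothesis compares.**

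| Hypothesis | Group | Compared with | Horizon |
|---|---|---|---|
| 1 | Observed | own course | 12 months |
| 2 | No treatment | own recruitment baseline | 3 months |
| 3 | Intervention | observed cohort | 12 months |
| 4 | Rescued controls | own earlier rate | after 3 months |

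No row sets intervention against no treatment.

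**3. Hypotheses 2 and 3 under an inert programme.** Assumptions, none of them from the protocol:
- both randomised arms decline by the same amount d, in SD units of the change score, and the observed cohort does not decline;
- there is one measure and one time point, so the 3 versus 12 month mismatch is not modelled;
- Hypothesis 2 is met if the control arm's one-sample t test (n = 50, two-sided 5%) shows significant decline;
- Hypothesis 3 is met if the intervention arm (n = 50) is not significantly worse than the observed cohort (n = 100).

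The two events involve different people, so P(both) = P(H2) × P(H3). P(H2) uses a noncentral t with parameter d√50. P(H3) uses one with parameter d / √(1/50 + 1/100).

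| d (SD) | P(H2) | P(H3) | Product | Simulation (4,000 runs) |
|---|---|---|---|---|
| 0 | 0.025 | 0.975 | 2.4% | 2.7% |
| 0.1 | 0.103 | 0.917 | 9.4% | 8.6% |
| 0.2 | 0.283 | 0.792 | 22.4% | 21.6% |
| 0.3 | 0.548 | 0.595 | 32.6% | 32.3% |
| 0.5 | 0.934 | 0.182 | 17.0% | 17.0% |

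In the same simulations a direct test of the randomised arms on one measure wrongly favoured the intervention in 2.4% to 2.7% of runs (nominal 2.5%), whatever the common decline.

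If Hypothesis 3 is instead read as no significant decline within the intervention arm, the simulated rates are 2.8%, 8.2%, 19.9%, 24.4% and 6.3%.

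**4. The overall three-level cohort test.** Take an inert programme, group sizes 100/50/50 and means (δ, 0, 0) in SD units. The grand mean is δ/2, so the noncentrality is 100(δ/2)² + 50(δ/2)² + 50(δ/2)² = 50δ². With F on 2 and 197 df at 5%:

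| High-low difference δ (SD) | Noncentrality | Chance of significance |
|---|---|---|
| 0.1 | 0.5 | 9% |
| 0.2 | 2.0 | 22% |
| 0.3 | 4.5 | 45% |
| 0.4 | 8.0 | 71% |
| 0.5 | 12.5 | 89% |

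A significant overall cohort effect therefore cannot by itself be read as an effect of the programme.

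**The case against.** The strongest reply is that the protocol never sets a success rule. The Hypotheses section predicts a course for each group, and nothing there says that meeting Hypotheses 2 and 3 establishes effectiveness. The abstract names the comparison with no intervention, the first study aim asks whether the intervention reduces decline, and the ANOVA contains the contrast. Naming a contrast inside a three-level factor is often left to an analysis plan, and none is shown. Figure 2, which illustrates the hypotheses, is not shown either.

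Much of this stands. A reader might infer that the trial cannot deliver its randomised comparison, or that it will declare an inert programme effective. The documents support neither: the model can give the contrast, and the success rule is implied at most. A reader might also infer that the three-level test is significant whenever high and low scorers differ, or that the false-positive rate is always far above 5%. The tables show otherwise: 9% for a 0.1 SD high-low difference, and about 3% for Hypotheses 2 and 3 together with no common decline.

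What the reply does not remove is that the hypotheses are set out in full and fix other comparisons. This is not detail lost in condensing. An analysis plan would normally implement the stated hypotheses, and these do not lead to the randomised contrast.

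**Conclusion.** The point holds as a defect in what the hypotheses state and what the analysis section leaves unnamed. The randomised comparison that the abstract gives as the RCT's purpose is missing from the hypotheses, and no section makes it the basis for the effectiveness conclusion.

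The size is conditional. If Hypotheses 2 and 3 were used as the success rule, the chance that an inert programme meets both on one measure runs from about 3% to 32% over assumed common declines of 0 to 0.5 SD, peaking near 0.3 SD among the values tried. The direct contrast stays at about 2.5%. The excess arises only if low scorers decline, which is what Hypothesis 2 predicts. Allowing any one of several measures, as Hypothesis 2 does, changes these figures further in a way that depends on correlations the protocol does not give.

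**What to change.** 1. In Hypotheses, add that change in the FD measures differs between the intervention and no-treatment arms.
2. In Analysis of data from Studies 1 and 2, name the intervention versus no-treatment contrast (cohort by time, the two randomised arms only, difference with 95% CI) as the basis for the effectiveness conclusion. Report it at three months after randomisation, the point used for sizing, and over the 12 months in the aims.
3. Label Hypotheses 1 to 3, and every comparison with the observed cohort, as descriptive.

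Resting effectiveness on three months alone would not fit the 12-month aims. Whether change is measured from recruitment or from the one-month value is a separate choice that this fix need not settle. It also does not settle which FD measure leads.

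The cost is wording; no new data, visits or arms are needed. The downside is that the effectiveness claim becomes harder to meet than under Hypotheses 2 and 3. Whether 50 per arm gives 80% power for the contrast cannot be confirmed until the SD behind the sample size is stated.

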### How is FD detected?

FD generally occurs subtly and can remain undetected until an unexpected and often catastrophic event occurs [6]. This can be a fall or unexplained ill health which requires hospitalization. This event, if followed by a comprehensive assessment, can expose the magnitude of an individual’s loss of capacity to function safely and independently [6,7,17].

There are a variety of ways of assessing FD; however, it is most commonly assessed as the capacity to complete basic and instrumental activities of daily living (ADLs and iADLs). Basic ADLs are everyday tasks (bathing, dressing, feeding, continence, transferring, toileting) [18], while iADLs are higher level activities (shopping, driving, banking and so on) [19,20]. Inability to manage ADLs safely and independently may only be temporary, if related to illness. This will usually respond well to recovery time and short-term targeted intervention. FD, however, may be irreversible if identified too late for effective community-based interventions. Individuals who have passed the critical threshold of FD may not be able to live safely at home despite intensive and long-term supports and, thus, may require permanent residential care. Irrespective of the point at which FD is assessed on its trajectory, there is no agreement on the best measures to detect FD nor the point of critical deterioration [21].

Detecting FD early and putting supports in place, as directed by the older person, to redress specific and individual areas of decline has been proposed as a way of maintaining older people’s community independence for a longer time [17,22-25]. Comprehensive frailty indices with multiple screening items have also been proposed from population research, mainly conducted in the UK and Canada [6,21,26,27]. However, there are few opportunities in Australia comprehensively to capture this amount of information from community-dwelling older people who are not in health crisis and who may not routinely come to the attention of the healthcare system. FD screening tools reported in the Australian literature are implemented at ‘point-in-time’, commonly during a health crisis at an ED presentation or hospitalization [28]. In these environments, assessment of FD may be inappropriate, when older people are unwell, disoriented, frightened and/or in unfamiliar environments. This raises issues of validity of assessment and/or reliability of responses.

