### Baseline screening

We will collect data in the ED (baseline) on consenting, eligible participants from

•the electronic hospital admissions system - age, gender, residential details, differential diagnosis; and

•a test battery as successfully piloted in our 2011 study [37]. This captures the highest level of schooling, primary language, ED presentations and hospitalizations in the past six months, falls in the past twelve months using the Falls Risk in Older People - Community (FROP_COM) instrument [39], living arrangements, requiring a carer, receiving community services, type and use of gait aid, iADLs[19] and cognition with the Mini Mental State Examination (MMSE) [40].

Based on data from our pilot study, we will additionally apply the Katz *et al*. [18] 20 basic ADL instrument and two quality of life measures – the SF12 [41,42] and the Australian Quality of Life (AQoL 4D) [43]. By collecting both basic and iADL scores, we can provide comprehensive ADL information about the target population to compare with international data. The SF12 provides the opportunity for international population-based comparisons of quality of life [41,42] with our sample of older ED presenters. The AQoL, which has not previously been used for older people discharged from ED, provides an Australian perspective on health-related multi-attribute utility quality of life [43], and allows production of health cost effectiveness data (quality-adjusted life years (QALYs)), and estimation of burden of disease.

This total test battery takes an average of 5.5 minutes to administer. All but two questions are delivered verbally by the recruiting researcher, who records the answers. The older person only has to write responses to two MMSE questions.

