### Outcome measures

At one, four, seven and thirteen months after recruitment, all participants will be contacted by telephone and consent sought for interview. Socio-demographic information will be confirmed, and all outcome instruments and mutable independent variables will be recorded (Table 1). Semi-structured questions will be asked about how participants are managing, their concerns and reasons for subsequent hospitalizations and ED presentations. At the four, seven and thirteen month data collection points (after nested RCT commencement), assessors will be blinded to group allocation.

**Table 1 T1:** Timeframes of outcome measurements

**Measures**	**Baseline**	**1 month**	**4 months**	**7 months**	**13 months**
ADLs	√	√	√	√	√
iADLs	√	√	√	√	√
SF12	√	√	√	√	√
AQoL_4D	√	√	√	√	√
Falls	√ (last 12 months)	√ (last month)	√ (last 3 months)	√ (last 3 months)	√ (last 6 months)
Hospitalizations	√ (last 6 months)	√ (last month)	√ (last 3 months)	√ (last 3 months)	√ (last 6 months)
Gait aid (type)	√	√	√	√	√
Living arrangements	√	√	√	√	√
Carer engagement	√	√	√	√	√
Organized (formal) community services	√	√	√	√	√
GP visits	√	√	√	√	√
Informal community supports	√	√	√	√	√
Satisfaction with community supports	√	√	√	√	√

ADLs, activities of daily living; AQoL_4D, Australian Quality of Life; GP, general practitioner; iADLs, instrumental activities of daily living; SF12, Short Form-12 Health Survey; √ indicates an occasion of data collection.

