### Study 1 analysis

FD will be assessed as change from baseline at each time point as:

•One or more falls increase from the baseline rate

•More than one event of hospitalization, or ED presentation, from the baseline rate

•Decrease of one point in any item of the ADL instrument [18], or

•Decrease of 2+ points from baseline total iADL score [19], or any decrease in baseline score in the domains of home activities, doing laundry, shopping and getting places (we previously reported these domains as critical to functional independence) [37]

•Scores decreasing from above median at baseline in either physical or mental domain, to below median in the SF12 [41,42]

•Any decrease in AQoL_4D (in the manner recently described for chronic obstructive pulmonary disease (COPD))[44]

•Change to a more assistive gait aid (for example, a one point stick to a four-pronged stick)

•Change in living arrangements to more supported care

•Increased carer involvement

•Greater type and frequency of use of formal community services or informal supports

•More frequent GP attendances.

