### Study 2: nested RCT

#### Subject selection and randomization

All participants in Study 1 will be stratified at one-month telephone follow-up into low and high scores on the MCS domain of the SF-12, (SF12-MCS), using the median cut point. We previously reported this as a transformed score of 55 [37], which is comparable to the same age-gender population SF-12 norms [41]. The nested RCT will be conducted involving only the subjects with lower than median SF12-MCS scores at this time point (Figure 1).

An independent trials office will randomize these subjects using a computer generated random number series, into an individualized person-centered community-based intervention, or ‘usual care’ which reflects no intervention. It is unlikely that any intervention would normally be offered to this population as it is not current practice to screen people for low mental component quality of life scores after an ED contact.

Considering Studies 1 and 2, there are three study cohorts (Figure 1):

•Subjects with SF12-MCS scores ≥55, who will be observed only, for 13 months after recruitment (12 months after the one month SF12 scores are taken) (the observed cohort)

•Subjects with SF12-MCS scores <55, from which two RCT groups will be allocated one month after recruitment, randomized into

•Intervention specifically tailored to address the individual’s problems, concerns, and goals (low SF12-MCS, intervention cohort)

•No treatment (low SF12-MCS, no treatment cohort).

Outcome measures for the two RCT groups will be taken at three-, six- and twelve-month time points after randomization (four, seven and thirteen months post-recruitment).

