### Ethical issues

Written permission has been obtained from the Hospital Executive and ED Management of the research site, and ethical approval has been granted by the Human Research Ethics Committee of the University of South Australia (Application ID: 0000031475).

While there are indications from its early evaluation data that the ECH intervention is acceptable to clients, its effectiveness is largely unproven, particularly in individuals with low SF12-MCS scores at commencement. We do not know that the intervention will provide any advantage; in fact, individuals may perceive that they are subjected to additional burdens, such as unwanted assessments and visitors in their home for (perhaps) no overall benefit. We see no disadvantage for the ‘control’ group (low SF12-MCS, no treatment cohort) at this point in our understanding, in not being offered care, nor not knowing that the intervention is available, as they are currently not offered routine intervention so early after an ED discharge. If ,however, at subsequent follow-up points (three, six or twelve months), any participant in the observed cohort arm or the low SF12-MCS, no treatment arm is identified as potentially demonstrating FD on any study measure, the need for rescue care will be suggested and ways to access this discussed. This may include attendance at their GP or making contact with local community service providers.

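### Hypothesis 4 claims a twelve-month window when only nine months are observed, and it judges rescue care against the early decline that selected the group

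*Protocol article*

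**What the plan says.** Hypothesis 4 (Hypotheses section) defines its group as members of the "no treatment cohort who demonstrate significant FD at three months follow-up, and who access ‘rescue’ intervention". It predicts that this group "will show an attenuated rate of FD over the following twelve months, compared with the rate they exhibited in the first three months".

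The visit schedule appears twice. Under Subject selection and randomization: "Outcome measures for the two RCT groups will be taken at three-, six- and twelve-month time points after randomization". Under Outcome measures: "At one, four, seven and thirteen months after recruitment, all participants will be contacted by telephone". Randomization takes place one month after recruitment, so the two clocks agree. The last contact is month 12 after randomization, which is month 13 after recruitment.

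FD is defined under Study 1 analysis as change from baseline, using eleven criteria. The iADL criterion is a fall of two or more points in the total, "or any decrease in baseline score in the domains of home activities, doing laundry, shopping and getting places". Baseline is the emergency department (ED) visit: "We will collect data in the ED (baseline) on consenting, eligible participants". Under Ethical issues, if an untreated participant at a follow-up visit "is identified as potentially demonstrating FD on any study measure, the need for rescue care will be suggested". The analysis section names three cohorts and no comparison group for rescued decliners.

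**The concern.** The window cannot be observed. No visit falls twelve months after the three-month follow-up.

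The comparison cannot isolate a rescue effect. The month-4 score does three jobs: it decides who enters the group, it ends the early rate, and it starts the later rate. Anyone whose month-4 score was low by measurement error or a passing illness will tend to show a steep early fall and a flatter later course. The article itself notes (How is FD detected?) that "Inability to manage ADLs safely and independently may only be temporary, if related to illness". Hypothesis 4 would count this pattern as support, so the trial could report that rescue slows FD when the same pattern is expected, to some degree, without any effect.

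Recovery from the index ED illness is not part of this concern. Baseline is taken during that illness, so recovering from it would make a participant less likely to be selected.

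**Working it through.** **Window (document figures only)**

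- Clock from randomization: 12 - 3 = 9 months.
- Clock from recruitment: 13 - 4 = 9 months.
- A true twelve-month window would need a visit at month 4 + 12 = 16 after recruitment. None is scheduled.
- If the phrase meant the trial's own year, the window would contain the three months it is compared with. The sentence fails on either reading.

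**Direction of the selection effect**

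Let each observed score be a stable true value plus an independent error with variance s². Selection is on D = y4 - y0, with Var(D) = 2s².

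- Early change: Cov(y4 - y1, D) = s², so its expected value is D × s²/2s² = D/2.
- Later change: Cov(y13 - y4, D) = -s², so its expected value is -D/2.

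The early rate is thus (D/2)/3 a month and the later rate is -(D/2)/9 a month. Because D is negative for everyone selected, error alone gives early loss and later gain.

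**Illustration 1: normal model, inert rescue**

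The article gives no SD. Its iADL sample size (difference 1.2, 50 per arm, 80% power, taken as two-sided 5%) implies SD = 1.2 / [(1.960 + 0.842) × √(2/50)] = 2.14. Test-retest reliability of 0.6 to 0.9 is assumed. Selection is a fall of at least 2 points from month 0 to month 4. Rates are points per month, as ranges over reliability.

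| Constant true loss per month | Month 1 to 4 | Month 4 to 13 |
|---|---|---|
| 0 | -0.39 to -0.50 | +0.13 to +0.17 |
| 0.10 | -0.43 to -0.54 | +0.01 to +0.05 |

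Check against the algebra at reliability 0.6 and no loss: mean D = -0.746 × 4 = -2.98. Then (D/2)/3 = -0.50 and -(D/2)/9 = +0.17, which agrees with the simulation.

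**Illustration 2: item model using the full iADL rule, inert rescue**

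Every input here is an assumption:

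- eight 0/1 items, four of them the named domains;
- misreport of 2%, 5% or 10% per item per call;
- true loss of 0, 1% or 2% per item per month;
- 80% or 90% of items independent at the start;
- loss rate equal for all or varying between people;
- half of those who qualify take up rescue, and they are tested with a paired t-test at two-sided 5%.

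Early rate = (y4 - y1)/3; later rate = (y13 - y4)/9.

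| Loss rate after month 4 | Later rate slower | Significant slowing |
|---|---|---|
| Unchanged | 30 of 30 scenarios | 29% to 53% |
| Doubled | not tabulated | 20% to 32% |
| Four times | 24 of 24 | 4% to 16% |
| Six times | 17 of 24 (6 reversed, 1 nil) | not tabulated |

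With the loss rate unchanged, 3.9 to 24.1 of 50 controls qualify, so rescued groups number about 2 to 12. Early rates are -0.22 to -0.39 and later rates -0.11 to +0.10. One example (5% misreport, 1% loss, 90% independent, equal rates): 14.7 of 50 qualify, the rate is -0.30 and then 0.00, and 45% of tests are significant.

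If only the faster-declining half take up rescue, the later rate is still slower in all 12 scenarios run (early -0.28 to -0.46, later -0.03 to -0.19).

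**Illustration 3: linear model, fall of 2+ points only**

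Error SD 0.5 to 1.25, loss of 0 or 1 point a year, slope SD 0 or 0.25 a month. The later rate is slower in all 16 settings. In the 11 settings where 3.9 to 10.3 of 50 qualify, groups of four are significant in 14% to 38%. Adding acceleration of 0.03 points/month² removes the slowing in 2 of the 16.

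**The case against.** - **The window is a slip of wording.** The schedule is clear elsewhere, and no sample size or visit depends on the phrase. Figure 2, which displays the hypotheses, is not available to check. This is true and limits the harm, but the sentence still needs correcting.
- **Hypothesis 4 is peripheral.** It is introduced as an addition and does not appear in the study aims. This stands, and it is why the point is not more serious. It remains one of four stated hypotheses.
- **Detail may sit in a fuller document.** An exploratory label or a caveat could be there. However, the hypothesis itself names the comparison rate, and a plan that followed it faithfully would inherit the bias.
- **Selection and reference periods overlap only in part.** FD is measured from month 0, while the first three months of the trial run from month 1 to month 4. This is correct: under independent errors, half of the selected drop falls outside the reference period. The calculations above use month 1 to month 4, so the reduction is already included.
- **The significance percentages rest on assumptions.** The paired test is not in the article, groups are small, and only one of eleven FD criteria is modelled. Criteria such as living arrangements or gait aid may be less prone to random misreport. This stands in full: the percentages show that the effect can matter and do not estimate it.
- **Net slowing is not guaranteed.** This also stands. Steep true acceleration removes or reverses it in some settings.

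**Conclusion.** The concern holds, and Hypothesis 4 is wrong as written. The window is nine months, not twelve; this follows from the schedule alone. The comparison uses the decline that selected the group as its yardstick, so the selection component always favours apparent slowing. That direction rests only on the month-4 score containing some error or transient illness. The size is unknown, because the article gives no iADL error SD. Under the assumed inputs with a constant loss rate, slowing appeared in every scenario without any rescue effect. In the item model it was lost only when loss after month 4 rose six-fold, and then in 7 of 24 scenarios. The randomized comparison of intervention with no treatment is not affected.

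**What to change.** Reword Hypothesis 4:

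1. Replace the twelve-month phrase with *nine months (month 3 to month 12 after randomization)*.
2. Label the hypothesis exploratory and non-randomized.
3. Add: *Some slowing relative to the first three months is expected from regression to the mean and will not be taken as evidence that rescue works.*

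If a contrast is wanted, describe rescued beside non-rescued decliners in the same arm over the same nine months. Both share the selection on early decline, but uptake is not random. When only the faster-declining half took up inert rescue in the item model, the rescued looked worse by 0.08 to 0.16 points a month. This table is therefore descriptive too.

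The cost is wording and, if used, one descriptive table. Visits, sample size, the randomized comparison and the offer of rescue care do not change.
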